**SECTION A**

**SECTION A**  
**STUDY OUTLINE**

**A.1 TITLE OF Study: Combating Maternal Mortality in Uganda: An assessment of the role of misoprostol in Prevention of Post-Partum Hemorrhage.**

**A.2 SUMMARY**

Explain why this study is being conducted, using lay terminology.

*Guidance note:*

*Please convey what you think is the importance of the research and WHY it is being carried out.*

Of the more than 500,000 peri-partum maternal deaths worldwide, 98% occur in developing countries (Hill et al, 2007; Khan et al, 2006). The maternal mortality rate in Uganda is among the highest in the world at 435 for every 100,000 women (UDHS, 2011) claiming the lives of over 5,500 mothers annually. Twenty-five percent of these deaths in Uganda occur due to postpartum hemorrhage (PPH) within 24 hours of delivery (MoH, 2012)

Oxytocin, a hormone that stimulates uterine contractions and helps control bleeding immediately after birth is the standard of care for prevention of PPH during the third stage of labor (WHO, 2010). The use of oxytocin, however, is limited by a number of factors including a requirement for trained personnel, cold chain storage, sterile syringes and needles for administration leading to inconsistent or no availability in some settings (Prata et al, 2013). Misoprostol, a synthetic prostaglandin with uterotonic properties has been proposed as an alternative strategy for prevention of PPH, because it is administered orally, has a long shelf life, and is stable at room temperature (Tang et al, 2002). A sub-lingual formulation is also available and enables a more rapid onset of action and greater bioavailability since it avoids first-pass metabolism (Katzung et al, 2007). Despite these advantages, sublingual misoprostol is not clearly the preferred agent because of insufficient information on its comparative efficacy with oxytocin for prevention of PPH in the management of third stage of labor (Tuncalp et al, 2012; Gulmezoglu et al, 2007).

[figure not shown]

In Uganda, up to 97.2% of health facilities expected to provide basic Emergency Obstetric Care do not offer them due to unavailability of electricity, laboratory services, trained staff (midwives) and medicines among others (Mbonye et al., 2006; 2007). Only 46% of the overall deliveries occur in presence of a skilled health worker in contrast to 95% attending at least one antenatal care (PATH, 2010; VSI, 2010; USAID, 2008; WHO, 1997) yet deaths due to PPH occurs within 24 hours following delivery due to excessive blood loss (Ronsmans& Graham, 2006; Khan et al, 2006; Li et al, 1996). Other authors have documented the share of births attended by skilled health personnel to be as low as 29% among the poorest within developing countries (USAID, 2008; UDHS, 2006). Majority of these women give birth at home (Knippenberg, 2005) with an estimated 18 million deliveries in Sub-Saharan Africa assisted by Traditional Birth Attendants (TBAs), a family member or alone (Lawn, 2005). The use of misoprostol on the other hand, which is cheap, does not require refrigeration and its heat stable properties has been shown to be effective in the prevention and management of PPH when used with or without controlled cord traction or uterine massage (Derman et al, 2006), a possibility of giving vast lifesaving hope in low resource setting.

We generally intend to document the role of misoprostol in management of third stage of labor in Uganda. In order to help resolve the question of efficacy in prevention of PPH, we intend to perform a double-blind, double-dummy randomized controlled trial of sublingual misoprostol versus oxytocin at Mbarara regional referral hospital, Uganda. In this trial, we hypothesize that sublingual misoprostol will be non-inferior to oxytocin because of its additional advantage of rapid onset of action and greater bioavailability compared to oral route.

### **A.3 OBJECTIVES**

List the major objectives/hypothesis, which have governed your choice of study design

*[PPH RCT Study protocol-version 2.0 June 18th 2012]*

[figure not shown]

## General objective

To examine the role of sublingual misoprostol 600µg in the management of third stage of labor in Uganda

## Specific objectives

1. To assess the efficacy of sublingual misoprostol 600µg, a prostaglandin E1 analogue as an alternative first-line uterotonic in prevention of PPH in Mbarara Regional Referral Hospital (MRRH), South Western Uganda
  - a) To compare maternal blood loss within 24 hours after delivery between misoprostol and oxytocin groups of mothers delivering at MRRH.
  - b) To compare the pre and post delivery changes in hematocrit and hemoglobin levels in the Misoprostol and oxytocin groups of delivering mothers at MRRH.
  - c) To determine the proportion of women who require additional therapeutic procedures or uterotonics in third stage of labor for treatment of PPH in the Misoprostol group.
  - d) To compare length of third stage of labour between the misoprostol and oxytocin groups of mothers delivering from MRRH
  - e) To determine the proportion of women with retained placenta between the two groups.
  - f) To compare the proportion of women requiring and getting blood transfusion between misoprostol and oxytocin groups.
2. To assess the safety (shivering, fever, headache, diarrhea, after pains, death, nausea/vomiting) of sublingual misoprostol 600µg as an alternative prophylactic uterotonic to oxytocin in the management of third stage of labor to prevent PPH.

## Hypothesis

Ho: 10 IU Oxytocin is significantly better than sublingual misoprostol 600µg in management of third stage of labor

H1: Sublingual misoprostol 600µg is non- inferior to 10 IU oxytocin and will not be more than 6% worse [than 10 IU oxytocin] in management of third stage of labor

[figure not shown]

#### A.4 METHODOLOGY

Outline how you intend to achieve the objectives of the study.

*Guidance notes:*

*For each objective/hypothesis:-*

- *define the target population*
- *describe how the sample(s) is(are) to be recruited from the target population(s)*

*Even if the main thrust of the research is biomedical, the rationale behind your use of social science methods (e.g. patient interviews) should be clear.*

*describe how the sample(s) is(are) to be recruited from the target population(s)*

[figure not shown]

Objective 1 and 2 will be achieved through a proposed non-inferiority trial of sublingual misoprostol 600µg. Following arrival of the laboring mothers at the maternity ward, mothers will be assessed and admitted. History will be reviewed to identify mothers eligible for vaginal delivery. Only mothers 38-41 weeks of amenorrhea admitted and anticipating vaginal delivery at MRRH will be eligible to participate in the study. Mothers with IUFD, hypertensive disorders, cardiac or coronary disease, inflammatory bowel disease, elective or previous Caesarean Section, gestation age < 38 weeks of amenorrhea and hypersensitivity to prostaglandins will be excluded from this study due to their associated risks to PPH (Chien, 1999; Combs et al, 1991).

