### **Randomization**

Consecutive numbers ranging from 001 to 1140 will be computer generated to indicate the two main groups into which mothers can be randomly assigned and enrolled. These consecutive numbers will be labeled on top of the opaque envelopes. Once eligibility of a mother is confirmed, they will be invited to participate in the study. The aim of the study and details of the procedures to be involved in the trial for both oxytocin and misoprostol groups, potential side effects and therapeutic benefits will be explained before randomization occurs. Once the mothers consent to participate in the study, a study number will be allocated by the midwife research assistant (**who will be recruited to work on the ward mainly for this study**) by taking the next in a series of similar opaque envelopes provided to conceal allocation of groups. These opaque envelopes will be labeled with computer-generated list of numbers with group allocation (either COHORT or Comparison Groups) of the mothers randomized in blocks of 10. Midwife research assistants will be blinded to the treatment group allocation and will open the envelope to prepare the treatments in the envelope provided and pre-packed by an independent pharmacy technician when vaginal delivery is eminent. This administration will be within one minute after delivery.

A first blood sample for complete blood count (CBC) will then be drawn immediately after admission and consenting of the eligible mothers to document Hemoglobin (Hb), hematocrit levels, MCV, blood group & cross matching (to document baseline values and assess need for transfusion). The second blood sample will be drawn at discharge or before blood transfusion to estimate pre-transfusion levels. The socio-demographic data and obstetric characteristics will also be documented. The patient will then be monitored for progress of labor. In case a consented mother ends up in theatre for caesarean section, the time and indication will be documented and excluded. A total of 1140 adult mothers will be enrolled for this study

[figure not shown]

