#### A.5.3 Describe how and where the participants are to be recruited?

*Guidance notes:*

*This is distinct from the statistical sampling method described in A.4. You should outline the procedures for recruitment of each group of participants, include details on:*

- the setting (e.g. Country, Town, District, on the ward, out-patient department, in the home)*
- inclusion and exclusion criteria for selection, if relevant (e.g. "Women of child-bearing age will be excluded")*

The Randomized Controlled Trial (RCT) study will purposively be carried out in the Maternity ward of Mbarara Regional Referral Hospital (MRRH), rural south western Uganda which also doubles as a Mbarara University Teaching Hospital for the faculty of medicine. The hospital is located in Kamukuzi Division, Mbarara Municipality along 30° 20'E' and 31°20'E longitude and 1°30'S and 0°30'N Latitude (DISH, 2011 <http://www.ugandadish.org/>). The regional referral hospital receives mothers from different tribal and socio-demographic locations in Uganda. Though inadequate, the hospital is equipped with trained staff, midwives, and obstetricians able to offer emergency obstetric care (EMOC) facilities. The Hospital also has good blood transfusion services and theatre for additional therapeutic procedures that may be required to treat PPH. Mothers received in this hospital may therefore represent different mothers from various social and demographic backgrounds.

[figure not shown]

Mothers with IUFD, hypertensive disorders, cardiac or coronary disease, inflammatory bowel disease, elective or previous Caesarean Section, gestation age < 38 weeks of amenorrhea and hypersensitivity to prostaglandins will be excluded from this study due to their associated risks to PPH (Chien, 1999; Combs et al, 1991). Mothers will be consented during early stages of active labor (before 6 cms of cervical dilation) to give ample time for mothers to think through the consent process and avoid feeling coerced. The consented mothers will then be randomly assigned different treatment groups. These mothers will be blinded to the study group allocated.

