#### **Control (COMPARISON) group**

The comparison group on the other hand will involve the standard/ gold procedure in the management of third stage of labor. Mothers will be given oxytocin 10 IU as the prophylactic uterotonic agent within one minute following delivery of the baby. This time according to Tharakan and Jha (2008) is more effective and safe compared to injection after delivery of placenta. This group will also receive a placebo taken sublingually to blind for misoprostol. This group will be the control group. Delayed cord clamping will also be preferred.

In all the two groups, the placenta will be delivered manually if not delivered after 30 minutes. In case bleeding persists, additional uterotonic agents, bladder emptying, expulsion of clots, blood transfusion or surgical procedures like hysterectomy will be used to manage PPH and this will be documented for all the groups.

Same sublingual route of administration will be preferred due to its pharmacodynamics properties including; rapid onset of action, greater bioavailability

[figure not shown]

and prolonged activity (Tang et al, 2002; Andolina, 2003; Hofmeyr, 2005; Khan, 2003; Abdel-Aleem, 2003). Similar misoprostol doses will also be maintained to avoid variations in plasma therapeutic levels (Mousa and Alfrevic, 2009, Tang et al, 2002). Single doses of recommended 600µg misoprostol will be used as opposed to repeated doses (FIGO/ICM, 2006).

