required to be confident that misoprostol is a reasonable alternative to oxytocin and of vital benefit compared to no intervention. A total of **1140** mothers will therefore be needed to achieve a 90% power (two sided) to say that misoprostol is no worse than oxytocin in PPH prevention. Each of the two groups, misoprostol and oxytocin will comprise of 570 mothers.

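### The hypersensitivity exclusion covers prostaglandins but not oxytocin, although every mother may be randomised to either drug and the injection is given blinded

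*Protocol*

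**What the plan says.** Protocol A.4 (Methodology) lists the exclusions: intrauterine fetal death, hypertensive disorders, cardiac or coronary disease, inflammatory bowel disease, and elective or previous caesarean section. It then closes with "gestation age < 38 weeks of amenorrhea and hypersensitivity to prostaglandins will be excluded". A.5.3 gives the same list in the same words: "gestation age < 38 weeks of amenorrhea and hypersensitivity to prostaglandins will be excluded from this study". Both places justify the whole list by the risk of PPH that these conditions carry.

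The only history review described in A.4 serves another purpose: "History will be reviewed to identify mothers eligible for vaginal delivery".

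Oxytocin is an active study drug. The Control (COMPARISON) group section states: "Mothers will be given oxytocin 10 IU as the prophylactic uterotonic agent within one minute following delivery of the baby". On numbers, A.5.4 states: "Each of the two groups, misoprostol and oxytocin will comprise of 570 mothers".

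On blinding, the Randomization section says: "Midwife research assistants will be blinded to the treatment group allocation and will open the envelope to prepare the treatments". The envelopes are pre-packed by an independent pharmacy technician. A.8.1 adds that the dummy injection and the sublingual placebo are packaged to look exactly like the real drugs.

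**The concern.** A mother should be randomised only if she can receive either treatment. The protocol writes this principle down for one study drug and leaves it unwritten for the other. A mother with a known reaction to a prostaglandin is kept out by rule. A mother with a known reaction to oxytocin meets every written criterion.

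Blinding makes screening the natural place to catch this. The envelope is opened when vaginal delivery is close, and the treatment is due within one minute of birth. The midwife who prepares it cannot tell from the pack whether the injection is oxytocin or the dummy. What is at stake is the safety of a rare individual mother, not the validity of the comparison.

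**Working it through.** **Inputs**

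- Exclusion for drug hypersensitivity: prostaglandins only (A.4 and A.5.3).
- Active drugs randomised: sublingual misoprostol, which the Specific objectives describe as a prostaglandin E1 analogue, and oxytocin (Intervention and Control group sections).
- Sample size: 1140 in total, 570 per arm (A.5.4).
- Randomisation: "of the mothers randomized in blocks of 10" (Randomization section).
- Non-inferiority margin: 6 percentage points (Hypothesis; A.5.4).

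**Step 1. Allocation probability.** P(oxytocin) = 570/1140 = 0.50. Two equal groups in blocks of 10 means 5/10 = 0.50 within each block. The plan's figures agree with each other.

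**Step 2. Coverage of the criterion.** Set the criterion against the two drugs:

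| Drug a mother may be randomised to | Known hypersensitivity excluded in A.4? | In A.5.3? |
|---|---|---|
| Misoprostol (prostaglandin analogue) | Yes | Yes |
| Oxytocin | No | No |

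No other section shown names oxytocin hypersensitivity. A mother with a known oxytocin reaction who meets the other criteria is therefore eligible, and has a probability of 0.50 of being allocated that drug.

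**Step 3. How many mothers.** The documents give no frequency, so the expected number cannot be derived from them. For scale only, if a proportion f of eligible mothers had a known reaction and none was declined, the expected number enrolled is 1140 × f and the expected number allocated oxytocin is 1140 × f × 0.50 = 570 × f.

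- Assumed f = 1/1000: 1.14 enrolled, 0.57 allocated oxytocin.
- Assumed f = 1/10,000: 0.114 enrolled, 0.057 allocated oxytocin.

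Both rates are assumptions, and the point does not depend on either.

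**Step 4. Effect on the primary outcome.** If the PPH outcome of one mother changed, her arm's proportion would move by 1/570 = 0.00175, about 0.18 percentage points. Against the 6-point margin that is 0.18/6, about 3%.

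**Step 5. Order of events.** In the Randomization section, eligibility is confirmed first, then consent is taken, then a study number is allocated. Every criterion, present or absent, therefore acts before the arms exist and applies to both equally.

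**The case against.** The strongest reply is that the usual safeguards still work at enrolment. Blinding hides the allocation. It does not hide the fact that any mother in the trial may receive oxytocin. History is reviewed, both drugs and their side effects are explained before randomisation, consent is sought early in labour to allow time, and senior obstetricians supervise. Staff can decline a mother with a known reaction, or she can decline. Oxytocin is also the standard prophylactic at this hospital (B.3.2), which may explain why only the less familiar drug was screened for. The attached consent form is not among the pages shown, so a screening question there cannot be ruled out.

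Most of this stands, and it keeps the point small. It does not close the gap. The same good sense would also keep out a mother who reacts to prostaglandins, yet the protocol writes that rule down. The two eligibility statements are where the matching rule belongs, and neither contains it.

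A reader might infer more than the text supports, in four ways:

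- *That exclusions differ between the arms.* They do not. Eligibility is fixed before randomisation, so the list affects who enters the trial and not the comparability of the groups.
- *That non-adherence or unblinding would fall in the oxytocin arm only.* A midwife who learns of a reaction while blinded would withhold or ask to unblind whichever arm the mother is in. Only the loss of active oxytocin would be confined to that arm.
- *That blinding removes the usual check.* It removes the check at the moment of injection. The check at history review and consent remains available.
- *That the PPH-risk rationale shows the criterion was not chosen with the study drugs in mind.* Misoprostol is a prostaglandin analogue, so the criterion plainly matches a study drug. The rationale closes a mixed list and is loosely worded; it says nothing about how this item was chosen.

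**Conclusion.** The point holds as a minor participant-safety gap. The written criteria screen for known hypersensitivity to one of the two randomised drug classes and not the other, while each mother has a probability of 0.50 of receiving either and the injection is prepared blinded. A mother with a known oxytocin reaction is eligible as the text stands, and nothing shown requires staff to decline her.

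There is no bias between arms and no material effect on the PPH estimate. The case is expected to be rare, but its frequency is not in the documents. The conclusion rests on A.4 and A.5.3 being the complete eligibility criteria; a screening question in the pages not shown would reduce the practical risk but would leave the written criteria incomplete.

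**What to change.** In A.4 and A.5.3, reword the criterion so that known hypersensitivity to either randomised study drug, misoprostol (or other prostaglandins) or oxytocin, is an exclusion. Every randomised mother can then receive either arm. State this criterion apart from the exclusions justified by PPH risk, with its own reason: inability to take a study drug.

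The cost is a few words in two places and one more screening question, with practically no loss of recruits. The sample size, randomisation and analysis are unaffected.

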### **Randomization**

Consecutive numbers ranging from 001 to 1140 will be computer generated to indicate the two main groups into which mothers can be randomly assigned and enrolled. These consecutive numbers will be labeled on top of the opaque envelopes. Once eligibility of a mother is confirmed, they will be invited to participate in the study. The aim of the study and details of the procedures to be involved in the trial for both oxytocin and misoprostol groups, potential side effects and therapeutic benefits will be explained before randomization occurs. Once the mothers consent to participate in the study, a study number will be allocated by the midwife research assistant (**who will be recruited to work on the ward mainly for this study**) by taking the next in a series of similar opaque envelopes provided to conceal allocation of groups. These opaque envelopes will be labeled with computer-generated list of numbers with group allocation (either COHORT or Comparison Groups) of the mothers randomized in blocks of 10. Midwife research assistants will be blinded to the treatment group allocation and will open the envelope to prepare the treatments in the envelope provided and pre-packed by an independent pharmacy technician when vaginal delivery is eminent. This administration will be within one minute after delivery.

A first blood sample for complete blood count (CBC) will then be drawn immediately after admission and consenting of the eligible mothers to document Hemoglobin (Hb), hematocrit levels, MCV, blood group & cross matching (to document baseline values and assess need for transfusion). The second blood sample will be drawn at discharge or before blood transfusion to estimate pre-transfusion levels. The socio-demographic data and obstetric characteristics will also be documented. The patient will then be monitored for progress of labor. In case a consented mother ends up in theatre for caesarean section, the time and indication will be documented and excluded. A total of 1140 adult mothers will be enrolled for this study

[figure not shown]

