#### **Intervention (COHORT) group**

The intervention group will be given sublingual misoprostol 600µg as part of the routinely done active management of third stage of labor within one minute of delivery. In this group, sublingual misoprostol 600µg will be administered as a prophylactic uterotonic agent. Delayed cord clamping will also be preferred due to documented benefits to the baby (Farrar 2009a; RCOG, 2009; Mc Donald, 2008; Van Rheen, 2007; Hutton, 2007; Chaparro, 2006; Ceriani et al, 2006; Rabe, 2004). Blinding will also be done by administration of 1 ml of normal saline to mimic oxytocin injection.

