## A.8 QUALITY ASSURANCE

A.8.1 What procedures are in place to ensure the quality of the data?

*Guidance notes:*

*For qualitative data (for example) what procedures will be used to check translations or compare data obtained from different sources?*

*For quantitative data (for example) how will transcription errors be minimised?*

*Give some detail on how methods are going to be piloted, if appropriate*

- An instrument to collect the required data has been adapted from the tools used by other researchers in other sites.
- Computer-generated numbers will be used to randomize mothers into this study. These numbers will be in opaque envelopes to blind the observers on the group to which the next mother will be randomized and observed. The Investigator or midwife researchers/ observers will not have prior knowledge of the treatment allocated to the next patient to avoid bias into the random allocation process.
- Double blinding will be done by administration of 1 ml of normal saline or water for injection to the misoprostol group to mimic oxytocin injection. **All the inactive agents (dummy oxytocin/ water for injection and placebo for misoprostol) will be packaged to exactly resemble the actual drugs themselves to ensure effective double blinding.** The comparison group on the other hand involving the standard/ gold oxytocin as a prophylactic uterotonic agent will also receive a placebo taken sublingually to blind for misoprostol.
- Details of the aim and procedures to be involved in the trial for both oxytocin and misoprostol groups, potential side effects and therapeutic benefits will be explained to the eligible patients on admission by the midwife researcher before consent and randomization occurs. Once the mothers consent to participate in the study, they will be monitored for labor and opaque envelopes containing computer-generated consecutive numbers from 001-1140 will then be opened once vaginal delivery is deemed inevitable.

[figure not shown]

- Improved routines at the labor ward will be targeted and all mothers on the ward regardless of the intervention will be treated similarly. A 'PPH Trolley' will be freely provided at all times in the labor ward to improve availability and accessibility of these uterotonics.

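### The Randomization text puts the unmasked group name on the envelopes, contradicting the concealment and blinding stated in the same paragraph and in A.8

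*Protocol*

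**What the plan says.** The Randomization text in A.4 describes the envelopes in three ways.

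- On the outside: "These consecutive numbers will be labeled on top of the opaque envelopes". No group is mentioned.
- On purpose: after consent, the midwife research assistant allocates a study number by "taking the next in a series of similar opaque envelopes provided to conceal allocation of groups".
- On the label again: the envelopes will be "labeled with computer-generated list of numbers with group allocation (either COHORT or Comparison Groups) of the mothers randomized in blocks of 10".

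The paragraph then adds: "Midwife research assistants will be blinded to the treatment group allocation and will open the envelope to prepare the treatments". The contents are pre-packed by an independent pharmacy technician.

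The two names on the label are defined under A.5.3. One subsection is headed "Intervention (COHORT) group" and describes sublingual misoprostol. The next uses the Comparison name for the oxytocin control arm.

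A.8 promises that "The Investigator or midwife researchers/ observers will not have prior knowledge of the treatment allocated to the next patient". It also says that the dummies look exactly like the active products and that the outcome assessors are blinded. On the study numbers A.8 differs from A.4: it places them inside the envelopes rather than on top.

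**The concern.** The label sentence has the envelopes as its subject and labelling as its verb, so whoever prints the 1140 labels has a written instruction to include the group. Opaque paper and look-alike dummies give no protection against an arm name on the outside.

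The exposure would fall on one role. The midwife research assistants explain the trial and obtain consent (B.5, item 5.2), take and later open the envelope and prepare the treatment (A.4), make the observations (A.6.1), and are trained to estimate and record blood loss (A.8). A.4 has the envelope taken once consent is given but opened only when delivery is near, so a legible label could be in view through much of labour.

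Foreknowledge of the arm opens the way to selective enrolment or reordering of envelopes. Knowledge of the arm after delivery can influence the estimation of spilled blood, which counts towards a primary outcome defined by a 500 mL threshold (A.5.4), and the decision to give additional uterotonics. In a non-inferiority comparison with a 6% margin, such biases can push the conclusion either way, and the analysis cannot repair them afterwards.

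The single stated block size of 10 is a second, smaller worry. If past allocations can be guessed, for example from shivering or fever, which A.3 lists as safety outcomes, the end of a block becomes predictable.

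**Working it through.** The protocol gives no figure for predictability, so there is none to reproduce. The check has two parts.

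**1. Can the statements be followed together?**

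| Statement | Place | If the group is on the label | If only the number is on the label |
|---|---|---|---|
| Envelope labelled with number and group | A.4, Randomization | followed | not followed |
| Consecutive number on the outside | A.4, Randomization | followed, with the group added | followed |
| Envelopes conceal allocation | A.4, Randomization | fails | followed |
| Midwife who opens the envelope is blinded | A.4, Randomization | fails | followed |
| No prior knowledge of the next treatment | A.8 | fails | followed |
| Outcome assessors blinded | A.8 | fails for the midwives who handle envelopes | followed |

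One sentence conflicts with four safeguards. The conflict depends on the names being unmasked, and A.5.3 confirms that they are.

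**2. How predictable is the next allocation?**

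Inputs: 1140 mothers (A.4), 570 per group (A.5.4), blocks of 10 (A.4). Hence 1140/10 = 114 complete blocks, each with m = 5 mothers per arm and C(10,5) = 252 possible orders.

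- *Group legible on the envelope:* 100% of allocations are known, whatever the block size.
- *Number only, double-dummy blind intact:* 50% are guessed correctly and 0% are certain. The block size makes no difference, because no earlier allocation is known.
- *Number only, every earlier allocation in the block known, block size known (assumed worst case):*
  - An allocation is certain once one arm in the block is full. The expected number per block is 2m/(m + 1) = 10/6 = 1.67, or 16.7%. Over the trial this is 114 × 10/6 = 190 of 1140.
  - Always guessing the arm with fewer mothers so far gives an expected number of correct guesses per block of m + 2^(2m−1)/C(2m,m) − 1/2 = 5 + 512/252 − 0.5 = 6.53, or 65.3%.
  - Enumerating all 252 orders gives the same 16.7% and 65.3%.

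For comparison, a fixed block of 4 under the same worst case gives 33.3% certain and 70.8% guessed correctly. A block of 10 is therefore not an especially weak choice.

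**The case against.** The strongest reply is that the label sentence is clumsy rather than operative. It may describe the computer list that links numbers to groups, in blocks of 10, and not what is printed on the paper. The surrounding text supports this. The same paragraph puts the numbers on top without a group, calls the envelopes similar, says they conceal allocation, and has an independent technician pack them. The double-dummy design and matched appearance would make little sense if the arm were written on the outside.

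Much of this stands. A reader might infer that the trial is to be run unblinded, or that its concealment is already defeated. The documents do not support that: they state the opposite intention several times, and one sentence contradicts them. The benign reading still does not remove the problem. The protocol as shown does not say who holds a linking list or that it stays off the ward, and A.4 and A.8 disagree on whether the numbers are on or in the envelopes. Staff would have to choose which sentence to follow.

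A reader might also infer that fixed blocks of 10 by themselves break the blind, or that about 190 allocations would in practice be known. Neither follows. The 190 requires every earlier allocation in the block to be known correctly, and the protocol works against that:

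- Envelopes are taken at consent, in early labour, so earlier mothers in a block may still be untreated when the next is taken.
- Mothers who go to caesarean section are excluded and may show no drug effect to read.
- Odd and even study numbers are divided between assistants.
- Nothing in the document shows that side effects identify an arm with certainty.

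Nor is blood loss mainly a matter of judgement. A.8 specifies pre-weighed pads, calibrated containers and cross-checked scales; spills are the part that is estimated, and staff are trained for it.

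**Conclusion.** The point holds as an internal contradiction in operative text. A.4 instructs that the envelopes be labelled with an unmasked group name, and elsewhere A.4 and A.8 make statements that such a label would falsify. Its size depends on which sentence staff follow: all 1140 allocations readable beforehand if the label sentence is taken literally, none if only the number is printed. The documents do not settle which was meant. The correction should come before envelopes are prepared, because broken concealment cannot be restored later.

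The fixed block size is a minor weakness. It has no effect while the blind holds, and its upper bound is 16.7% certain allocations (190 of 1140), assuming all earlier allocations and the block size are known. The documents give no basis for putting a figure on any resulting bias in the PPH comparison.

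**What to change.** Reword the Randomization paragraph in A.4 to say three things: each envelope and everything in it carries only the sequential study number; the list linking number to group is held off the ward by the independent pharmacy technician who packs the envelopes; and no one who enrols, treats or assesses mothers has access to it. Align A.8 with this, including whether the number is on the envelope or inside it.

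As a minor addition, replace the constant block of 10 by randomly varying block sizes, with the sizes kept out of any document available to ward staff.

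The cost is small. The wording change affects two sections and requires new labels only if group-bearing ones have been printed. Varying the blocks means regenerating the list before the start, and the final split may differ from 570/570 by a few mothers.
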